### Randomization

After informed consent is given and the initial assessment is completed, each participant is randomly allocated to either receive FBSFT immediately (arm A) or following one year of TAU (arm B). The randomization is performed by the pediatrician and allocation to the two groups is done by extracting a random, sealed envelope from a sealed folder. At the beginning of the study, there were 120 sealed envelopes: 60 with the letter A (for arm A) and 60 with the letter B (for arm B).

## Outcome measures

Measurement points are pre-treatment, post-treatment (i.e., 6 months from pre-treatment), at 12 months, 18 months and 24 months. See Fig. 1 for overview.

### Anthropometrical measures

Trained assessors at the OOC will measure height and weight for calculation of BMI (kg/m2), WC and body composition (measured with bio impedance (BIA), InBody 720). BMI will be converted to SDS using the extended IOTF [41, 44] BMI references. The percentage of the IOTF 25 threshold (%IOTF-25) is calculated as 100*(BMI/IOTF 25), where BMI is the child’s weight divided by height squared (kg/m^2^), and IOTF 25 is the BMI that corresponds to the IOTF threshold for overweight for the child’s age and sex. Dual-energy X-ray absorptiometry (DXA)-scans for determining the distribution of fat and muscle tissue will be conducted at the Department of Rheumatology at Haukeland University Hospital.

### Physiological measures

Blood samples will be drawn in the morning after an overnight fast and include measurements of total-cholesterol, high density lipoprotein (HDL), low-density lipoprotein (LDL), triglycerides (TG), aspartate transaminase (ASAT), alanine transaminase (ALAT), creatinine, glycated hemoglobin (HbA1c) and fasting insulin, c-peptide and glucose, thyroid stimulating hormone (THS), free thyroxine (fT4), and C-reactive protein (CRP). A bio-bank for the storing and registering of biological materials has been approved. Trained assessors at the OOC will measure blood pressure.

### Physical activity and sleep patterns

Physical activity and sleep patterns will be measured using Actiwatch 2 (Phillips). The actiwatch devices are wrist-worn accelerometers that records all uni-axial movement over 0.05G in thirty-second epochs. The actiwatch will be worn on the non-dominant wrist for seven consecutive days. A wrist-worn accelerometer was chosen over hip-worn accelerometers to ensure compliance [45]. Wrist-worn accelerometers are validated for use both as a measure of physical activity, inactivity and sleep and are recommended for use in studies evaluating lifestyle interventions for obesity among children and adults [46–48].

### Psychological measures

The following five questionnaires will be used in the study:

*The Child Behavior Checklist (CBCL)* [49], a 138-item scale assessing behavioral and emotional symptoms in children that has both a child/youth and parent form. Several studies have provided evidence of the instruments psychometric properties and stability [49–51].

*Children’s Depression Inventory (CDI)* [52], a 27-item self-report measure assessing the cognitive, affective and behavioral symptoms of depression in children (7–17 years). The psychometric properties of the scale have generally been found to be acceptable [53, 54].

*Self-Perception Profile for Children (SPPC)* [55], a self-report measure of self-perception or self-esteem in children aged 8 to 14 years widely used for research purposes. The questionnaire includes 36 statements and the children are asked to evaluate to which degree the statement fits their thoughts about themselves. The internal reliability has been demonstrated to be high [56].

*The Dutch Eating Behavior Questionnaire Child version (DEBQ)* [57], a measure of disordered eating behaviors in children and youth. DEBQ consists of three sub-scales: emotional eating, external eating, and restrained eating. The questionnaire is increasingly used for research on youth with overweight and psychometric properties have in general been found acceptable [58, 59].

*The Youth Eating Disorder Examination-Questionnaire (YEDE-Q)* [60], a self-reported measure of eating patterns and eating disorder psychopathology. The YEDE-Q is a self-report version of the Child Eating Disorder Examination (ChEDE) and was designed to include measurements of binge eating in youth [61]. The YEDE-Q has been validated using the ChEDE as an assessment of eating-related pathology in overweight youth [61].

### Other measurements

*Barriers to treatment participation scale (BTPS)* [62], a 44-item scale developed and validated to address drop-out from treatment with out-patient psychological treatment of children and adolescents. The scale is found to yield high levels of internal consistency and to be predictive of treatment dropout and weeks spent in treatment [62, 63].

*The Parenting Scale (PS)* [64], 30-item questionnaire designed to measure different parental disciplines with children and youth. The scale is widely used for research and clinical purposes. The internal consistency and test-retest stability have been found to be acceptable to good, and the validity of the instrument has been demonstrated in several studies [65, 66].

## Planned data analysis

A two-way MANOVA with one repeated-measure factor (Time: pre-intervention/post-intervention), and one between-group factor (Treatment Group: FBSFT vs. TAU) will be conducted to assess the impact of treatment on primary and secondary outcomes.

A one way within-subjects MANOVA will be used to analyze the effect of time (pre-treatment, post-treatment, 12-, 18-, 24 months post treatment) on primary and secondary outcomes.

In order to identify factors associated with treatment success and treatment drop out, multiple regression analyses will be conducted. The dependent variables are %IOTF-25 and drop-out status (yes/no). The predictors are: both parents participating in treatment, parental marital status, self-reported parental weight, socio-economic status and social network, psychological comorbidities.

In order to identify barriers to treatment and how these barriers influence children’s and parents’ treatment response, multiple regression analyses will be conducted. The dependent variable is %IOTF-25. The predictors are: competing activities/life stressors, relevance of treatment, treatment issues (logistics) and critical events.

Intention-to-treat analyses will be conducted and effect sizes calculated for treatment effects.

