**Methods:**

Randomized controlled trial (RCT), in which families (*n* = 120) are recruited from the children and adolescents (ages 6–18 years) referred to the Obesity Outpatient Clinic (OOC), Haukeland University Hospital, Norway. Criteria for admission to the OOC are BMI above the International Obesity Task Force (IOTF) cut-off ≥ 35, or IOTF ≥ 30 with obesity related co-morbidity. Families are randomized to receive FBSFT immediately or following one year of TAU. All participants receive a multidisciplinary assessment. For TAU this assessment results in a plan and a contract for chancing specific lifestyle behaviors. Thereafter each family participates in monthly counselling sessions with their primary health care nurse to work on implementing these goals, including measuring their weight change, and also meet every third month for sessions at the OOC. In FBSFT, following assessment, families participate in 17 weekly sessions at the OOC, in which each family works on changing lifestyle behaviors using a structured cognitive-behavioral, socio-ecological approach targeting both parents and children with strategies for behavioral maintenance and sustainable weight change.

Outcome variables include body mass index (BMI; kg/m^2^), BMI standard deviation score (SDS) and percentage above the IOTF definition of overweight, waist-circumference, body composition (bioelectric impedance (BIA) and dual-X-ray-absorptiometry (DXA)), blood tests, blood pressure, activity/inactivity and sleep pattern (measured by accelerometer), as well as questionnaires measuring depression, general psychological symptomatology, self-esteem, disturbed eating and eating disorder symptoms. Finally, barriers to treatment and parenting styles are measured via questionnaires.

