	10	A healthy peer environment; communicating with peers about new and healthy habits
	11	Taking on Teasing
3. Community Contex	12	Physical activity and the assessment of RED food in the environment/neighborhood
	13	To be active in your neighborhood; join groups or teams; to elicit support for healthy habits in your neighborhood/environment
	14	To fight weight stigmatization; influences from the media; to build a positive self-image and body image
	15	High risk situations (restaurants and fast food); to focus on healthy habits at school and work
4. Cross-contextual	16	To plan for healthy habits; relapse prevention and consolidating skills across different contexts
	17	Reviewing goals and skills; ending well; planning ahead

Through the treatment sessions, the families are taught a set of behavioral and cognitive techniques for promoting healthy behavior change and dealing with mechanisms that maintain unhealthy lifestyle behaviors:Self-monitoring. Both the parents and children monitor their eating, weight and activity on a week-to-week basic going through the intensive treatment phaseGoal setting, planning and reward systemsStimulus controlEmotion regulation strategiesReframing negative automatic thoughtsCommunication and interpersonal skillsParenting strategiesHealthy modeling from the parentsHealthy methods of self-evaluation and self-assertion

After the intensive treatment phase, the families receive monthly follow-up treatment for 18 months through collaboration between specialty and primary care: monthly follow-up sessions with their school nurse (primary care) and follow-up sessions every third month at the OOC. The focus for these sessions is maintenance of healthy habits.

For families assigned to standard treatment (treatment as usual, TAU), the treatment consists of a post-assessment meeting between a health care worker at the OOC and the family, agreeing on behavioral goals for changing lifestyle, a plan for the implementation of new behaviors and goals for weight loss. Each family also participates in monthly counselling session with their local health care nurse to work on implementing these goals, including measuring their weight change, and also meets every third month for sessions at the OOC for assessments, evaluation of progress and revision of goals. TAU is delivered over the course of 12 months.

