### Study objectives and hypotheses

The objectives and hypotheses of the current study are:To evaluate the effect of FBSFT compared to TAU for severe childhood and adolescent obesity in a common health care setting. The primary outcome is weight status, assessed as BMI, BMI standard deviation scores (SDSs) and percentages above the IOTF cut-off for overweight (%IOTF-25) [41]. Secondary outcomes are other weight-related anthropometric measurements (waist circumference (WC) and Waist-to-height ratio (WHtR) and corresponding SDSs), body composition (BIA, DXA), blood test, blood pressure, eating habits, sleep, physical activity as well as psychological well-being and parenting style.○ We hypothesized that FBSFT will be superior to TAU in improving these parameters both during the intensive treatment period and during the follow-up period.
To identify predictors of treatment success and treatment drop out with a focus on family variables, socioeconomic status, social network and mental health.○ We expect children from families in which both parents participate in treatment to demonstrate better weight loss outcome and have lower dropout rate.○ We expect children of parents living together to demonstrate better treatment effects and have lower dropout rate.○ We expect that parental (self-reported) weight status will influence treatment effects and dropout rate; higher BMI category will predict poorer treatment effects and higher dropout rate.○ We expect that lower socio-economic status and limited social network will predict poorer treatment effects and higher dropout rate.○ We expect poorer treatment effect and higher dropout rate among participants with psychological comorbidities.
To evaluate experienced barriers to treatment, and how these factors influence children’s and parents treatment response. Barriers to treatment are classified into four groups: competing activities/life stressors, relevance of treatment, treatment issues (logistics) and critical events.○ We expect lower degree of competing activities/life stressors to predict better treatment response and lower dropout rate.○ We expect higher degree of experienced treatment relevance to predict better treatment response and lower dropout rate.○ We expect lower degree of treatment issues and lower number of critical events to predict better treatment response and lower dropout rate.

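### The only listed analysis of the 12-, 18- and 24-month visits is a five-level omnibus test of time, and its significance cannot show whether improvement was retained

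*Protocol article*

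**What the plan says.** All places are in the protocol article.

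- **Outcome measures** sets five visits: "Measurement points are pre-treatment, post-treatment (i.e., 6 months from pre-treatment), at 12 months, 18 months and 24 months".
- **Planned data analysis** compares the arms with "A two-way MANOVA with one repeated-measure factor (Time: pre-intervention/post-intervention), and one between-group factor (Treatment Group: FBSFT vs. TAU"). That analysis stops at post-treatment.
- The same section then gives the one analysis that names the later visits: "A one way within-subjects MANOVA will be used to analyze the effect of time (pre-treatment, post-treatment, 12-, 18-, 24 months post treatment"). It has no group factor, and no contrast, direction or reference visit is named.
- The two regression analyses in that section give no time point for %IOTF-25. The closing line, "Intention-to-treat analyses will be conducted and effect sizes calculated for treatment effects", does not define a follow-up contrast either.
- **Study objectives and hypotheses** frames the follow-up claim between arms: "We hypothesized that FBSFT will be superior to TAU in improving these parameters both during the intensive treatment period and during the follow-up period".
- Maintenance appears as treatment content. The abstract speaks of "strategies for behavioral maintenance and sustainable weight change", and the Intervention section says of the 18 months of follow-up sessions: "The focus for these sessions is maintenance of healthy habits".

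**The concern.** The question of interest at the late visits is whether any improvement remains, and how much has been lost since the end of intensive treatment. The named test asks something else: whether any of the five visit means differs from any other. A fall between pre-treatment and month 6 is enough to violate that null. The test has no direction and no target visit, so a significant time effect is compatible with full maintenance, partial regain or a complete return to baseline.

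If a significant time effect over 24 months were reported as evidence of a lasting change, the long-term conclusion could rest entirely on the 6-month change. This applies within FBSFT families and to age-standardised outcomes, so it is separate from the missing group factor and from growth in raw BMI.

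**Working it through.** **Inputs from the article (Sample size).** 60 families per arm; correlation 0.5 between measurement points; alpha 0.05; power 0.80.

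**The plan's own figures.** For the group-by-time interaction with k = 2 groups and m = 3 time points, noncentrality is λ = f²·N·m/(1 − ρ), with degrees of freedom (k − 1)(m − 1) and (N − k)(m − 1). For f = 0.10, 0.25 and 0.40, the stated N of 164, 28 and 12 give power 0.805, 0.812 and 0.810. The stated sizes are reproduced. They concern the interaction, not the five-visit time test.

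**Assumptions for the time test.** One outcome with SD 1, n = 60, no dropout, and a loss d at month 6 of 0.2, 0.3 or 0.5 SD. The article gives no SD or expected loss, so d is shown as a range. Extending 0.5 from three time points to five is also an assumption.

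**Formula.** For one outcome, the within-subjects MANOVA test of time is Hotelling's T² on four differences, referred to F(4, n − 4). Under constant correlation, λ = n·Σ(μⱼ − μ̄)²/(1 − ρ).

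**Mean profiles at months 0, 6, 12, 18, 24 and their sums of squares.**

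- Maintained (0, −d, −d, −d, −d): 0.8d²
- Half regained by month 12, all by month 18 (0, −d, −d/2, 0, 0): 0.8d²
- All regained by month 12 (0, −d, 0, 0, 0): 0.8d²
- Linear regain to month 24 (0, −d, −2d/3, −d/3, 0): 0.756d²

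At d = 0.3, the first three give λ = 60 × 0.8 × 0.09/0.5 = 8.64. Linear regain gives 60 × 0.756 × 0.09/0.5 = 8.16.

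**Rejection rates, n = 60, constant ρ = 0.5.**

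| Profile | d = 0.2 | d = 0.3 | d = 0.5 |
|---|---|---|---|
| Maintained | 28.4% | 60.1% | 97.8% |
| Half by 12, all by 18 | 28.4% | 60.1% | 97.8% |
| All regained by 12 | 28.4% | 60.1% | 97.8% |
| Linear regain to 24 | 27.0% | 57.3% | 97.0% |
| 24 months minus pre-treatment, maintained | 33.2% | 62.8% | 96.8% |
| 24 months minus pre-treatment, any of the regain profiles | 5% | 5% | 5% |

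Simulation with 20,000 runs at d = 0.3 agrees for the omnibus test: 60.1% maintained, 60.2% regained by month 12.

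**Other correlation structure.** With correlation that decays over visits (AR(1)), d = 0.3 and n = 60:

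| Profile | AR(1) 0.5 | AR(1) 0.8 |
|---|---|---|
| Maintained | 44.7% | 82.8% |
| Half by 12, all by 18 | 50.6% | 93.1% |
| All regained by 12 | 60.7% | 98.0% |
| Linear regain to 24 | 47.3% | 90.0% |

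Under decaying correlation, each regain profile is rejected more often than full maintenance. The 24-month contrast also loses power there: its variance per family, 2(1 − ρ), rises from 1 at ρ = 0.5 to 2(1 − 0.5⁴) = 1.875 under AR(1) 0.5. Its rejection rate when nothing is retained stays at 5%.

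**The case against.** **Contrasts after an omnibus test are usually left to the analysis plan.** This is fair. The plan is not shown, and the article is condensed. A reader might infer that the trial cannot address maintenance at all; the documents do not support that. Contrasts may be specified elsewhere, and reported visit means would show regain. What stands is narrower: the article does name a test for these visits, and its significance does not bear on retention.

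**Maintenance is not a listed objective.** Also fair. The follow-up hypothesis is between arms ("superior to TAU in improving these parameters both during the intensive treatment period and during the follow-up period"), and the maintenance wording describes treatment content. The article does not say that the omnibus p-value will support a durability claim. However, arm B starts FBSFT after one year, so at 18 and 24 months there is no longer a comparator without FBSFT. Within-family change is what those visits can chiefly inform, and this is the test assigned to it.

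**The equality of rejection rates depends on the profile.** Correct. It is exact only for certain profiles under constant correlation. With full regain between months 12 and 18, the test rejects 79.9% at d = 0.3 against 60.1% for maintenance; with linear regain it rejects slightly less.

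**This is not type I error inflation.** Correct. In every regain profile the means do differ, so rejection is right for the null tested. Comparing 28% to 98% with the nominal 5% would misdescribe it as a false-positive rate.

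**The late visits are not confined to this one test throughout the article.** The Sample size section sizes an interaction that includes a 12-month point. The word only therefore applies to Planned data analysis, and the two sections need reconciling.

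**Conclusion.** The point holds in a limited form. In Planned data analysis, the late visits are tied by name to a single omnibus test of time, and a significant result does not distinguish retained from regained loss. With one outcome, 60 families, no dropout and constant correlation 0.5, it rejects 28%, 60% and 98% for losses of 0.2, 0.3 and 0.5 SD, whether the loss is maintained or regained by month 18 through half regain at month 12. Linear regain gives 27%, 57% and 97%. Under AR(1) correlation the regain profiles examined are rejected more often than maintenance. Loss size, correlation pattern and absence of dropout are assumptions, and the article does not say whether the arms are pooled in this test.

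The test itself is valid. The weakness lies in using it as the basis for a lasting-effect statement. It should be corrected, but it does not touch the 6-month comparison between arms.

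**What to change.** In Planned data analysis:

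1. Keep the five-visit time effect as a descriptive analysis.
2. Base any statement on lasting within-family change on two pre-specified contrasts on %IOTF-25, each with a 95% confidence interval. The first, tested first, is 24 months minus pre-treatment; claim a lasting change only if its interval excludes zero in the direction of improvement. The second is 24 months minus post-treatment; read the extent of regain from the interval, not from a non-significant p-value.
3. Apply these in arm A. In arm B, use only visits that exist after its start of FBSFT. The article does not show that a 24-month visit counted from that start is scheduled.
4. State that the contrasts are uncontrolled within-group changes and do not test the between-arm follow-up hypothesis.
5. Reconcile the section with the interaction in Sample size that includes a 12-month point, and with Outcome measures on visit timing. Outcome measures places post-treatment 6 months from pre-treatment and then lists 12, 18 and 24 months; Planned data analysis labels those months as post treatment.

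The cost is a change of wording. In arm A it uses visits already scheduled and needs no extra families. Under the constant-correlation assumption at d = 0.3, the first contrast has similar power to the omnibus test for a maintained loss: 62.8% against 60.1% with n = 60, and 90.3% against 92.2% with n = 120. The small downside is that the follow-up result may look less favourable than a significant omnibus time effect.

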### Sample size

One hundred twenty families will be recruited, with 60 families in each treatment arm. Power estimates were calculated using G*Power, version 3.1.3. [42, 43] With two treatment groups (TAU, FBSFT), 3 measurement points (pre-treatment, 6 months post-treatment and 12 month post-treatment) and a correlation of 0.5 between the measurement points, alpha .05, power .80, a small (*f* = 0.10), moderate (*f* = 0, 25) and high (*f* = 0.40) effect size would demand respectively sample sizes of 164, 28 and 12 participants to detect a significant group X time interaction on the primary outcome. For regression analysis of predictors of treatment outcome, a small to moderate effect size is expected (*f* = 0.15), and when testing the increase in R^2^ by adding 1 predictor to an analysis including 5 predictors in total, a sample size of 55 persons will be needed.

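### The MANOVAs appear to test primary and secondary outcomes together, which does not isolate weight status and can cost much of the power to detect a change in it

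*Protocol article*

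**What the plan says.** Planned data analysis names two MANOVAs. The first is a two-way MANOVA with time (pre- and post-intervention) and treatment group, for the impact of treatment on primary and secondary outcomes. The second covers all five measurement points: "A one way within-subjects MANOVA will be used to analyze the effect of time", with the levels and outcomes given as "pre-treatment, post-treatment, 12-, 18-, 24 months post treatment) on primary and secondary outcomes".

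Study objectives and hypotheses defines the outcomes. On the primary: "The primary outcome is weight status, assessed as BMI, BMI standard deviation scores (SDSs) and percentages above the IOTF cut-off for overweight (%IOTF-25". The secondary list includes "waist circumference (WC) and Waist-to-height ratio (WHtR) and corresponding SDSs), body composition (BIA, DXA), blood test, blood pressure, eating habits, sleep, physical activity", and adds psychological well-being and parenting style. Later sections break some of these into components. Physiological measures, for example, names 14 blood analytes, among them "aspartate transaminase (ASAT), alanine transaminase (ALAT), creatinine, glycated hemoglobin (HbA1c) and fasting insulin, c-peptide and glucose".

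Sample size states: "One hundred twenty families will be recruited, with 60 families in each treatment arm". Its calculation concerns a group by time interaction on the primary outcome.

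**The concern.** A MANOVA on several outcomes asks whether any combination of them differs. If weight status goes in with blood tests, sleep and questionnaire scores, the test no longer addresses the primary question alone. A significant result could come from a secondary outcome. A non-significant one could hide a real weight effect among outcomes that did not move. The trial would then lack a clear test of the question it was sized for.

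For the five-visit analysis there is a second issue. Each outcome brings four time contrasts, so a fully multivariate test over many outcomes may need more contrasts than there are degrees of freedom. Fallback choices (which outcomes to drop, how to group them, which form of the test to use) could then be made with the data in hand.

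**Working it through.** **The plan's own figure.** Inputs from Sample size: two groups, three measurement points, "a correlation of 0.5 between the measurement points, alpha .05, power .80". With N families, k = 2 groups, m = 3 times and correlation ρ = 0.5, the noncentrality is λ = f²·N·m/(1−ρ), with (k−1)(m−1) = 2 and (N−k)(m−1) degrees of freedom. For f = 0.10, 0.25 and 0.40 this gives N = 164, 28 and 12 (power 0.805, 0.812, 0.810). The article says that these effects "would demand respectively sample sizes of 164, 28 and 12 participants", so its figures reproduce. They come from a formula for one outcome, not for a joint test.

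**How many outcomes.** The article gives no count.
- Taking the objectives item by item: 3 primary variables + 13 secondary items = 16. The 13 are four waist measures, BIA, DXA, blood test, blood pressure, eating habits, sleep, physical activity, psychological well-being and parenting style.
- Expanding to individual measures: 3 weight + 4 waist + 2 body composition + 14 analytes + 2 blood pressures + 2 (sleep, activity) + 8 questionnaire scores = 35. The 8 are three DEBQ sub-scales and one score each for CBCL, CDI, SPPC, YEDE-Q and the Parenting Scale. Two blood pressures and one score for each of those five instruments are assumptions.
- Using more sub-scales would raise the count further.

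**Power of a joint between-arm test.** With two visits there is one change score per outcome, so the interaction test for p outcomes is a two-sample Hotelling T² on the changes. With 60 per arm, λ = (60·60/120)·Δ² = 30Δ², where Δ² is the squared Mahalanobis distance, and the degrees of freedom are p and 119 − p. For one outcome, 80% power at two-sided 0.05 needs a standardised difference in change of d = 0.516, so λ ≈ 7.98. This d is chosen to give 80% and is not a document figure.

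| Scenario (correlations are between change scores) | p = 1 | p = 16 | p = 35 |
|---|---|---|---|
| One outcome affected, others unaffected, uncorrelated: λ = 7.98 | 80% | 31% | 18% |
| All affected equally, correlation 0.5: λ = 7.98·p/(1 + 0.5(p−1)) | 80% | 59% (λ = 15.0) | 37% (λ = 15.5) |

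The opposite case also exists. If all outcomes improved equally and were uncorrelated, λ would be 7.98·p, about 128 at p = 16, and the joint test would gain power. That does not suit these outcomes, because BMI, BMI SDS, %IOTF-25, waist measures and body composition overlap.

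**Limit on the five-visit test.** Five visits give 4 contrasts per outcome. The fully stacked test needs 4p ≤ N − 1.
- 120 complete families: 119/4, so at most 29 outcomes. With 30, the 120 contrasts exceed 119 degrees of freedom and the covariance matrix is singular.
- 60 complete families (one arm): 59/4, so at most 14 outcomes.
- 16 outcomes: 64 contrasts, which fit at N = 120 (denominator df 119 − 64 + 1 = 56) but not at N = 60.
- 35 outcomes: 140 contrasts, which do not fit at N = 120.
- Averaged form (a sphericity-type assumption across visits): error df 119·4 = 476 against dimension 35, so it can be computed.

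**The case against.** The strongest reply is that no all-outcome model is written. "Within-subjects MANOVA" is also the usual name for the multivariate approach to repeated measures on a single outcome, with 4 contrasts against 119 degrees of freedom. The sample size uses a single-outcome formula, and the planned regressions take one dependent variable at a time. A condensed article may leave the grouping of outcomes to the full protocol or SAP.

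Part of this stands. The text does not say that every outcome enters one matrix. But the single-outcome reading fits the between-arm analysis poorly: with only two time levels, a MANOVA on one outcome reduces to an ordinary ANOVA. Naming a MANOVA there implies several outcomes together, and primary and secondary are named in the same sentence. That is a stated choice of method, not merely an omitted detail.

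A reader might go further and infer that the five-visit analysis cannot be computed even with complete data. The documents do not support that. It requires about 35 outcomes, a count the article does not give; every measure taken at all five visits, although the flow sheet that gives the overview is not available here; and the fully stacked form, which is not named. With the 16 listed items, with separate or domain-wise MANOVAs, or with the averaged form, the analysis runs at N = 120.

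The first row of the power table can fairly be called artificial, since the plan expects improvement in all parameters. The second row assumes equal improvement throughout and still shows a clear loss.

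**Conclusion.** The point holds in a limited form. As worded, both MANOVAs appear to test primary and secondary outcomes together, and such a test cannot show by itself that weight status changed. On the assumptions shown, 80% power for one outcome becomes about 31% to 59% with 16 outcomes and about 18% to 37% with 35. The size depends on the number of outcomes, their correlations and how many respond; only the sample size and alpha come from the article. The ceiling of 29 outcomes with 120 complete families (14 with 60) is a conditional limit on one form of the five-visit test. With a count anywhere from about 16 to 35 or more, it is a reason to fix the specification, not proof of an impossible analysis.

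**What to change.** Analyse each outcome in its own repeated-measures model, with the weight-status variables first and separately from the secondary outcomes. For the between-arm question use group, visit and group by visit. For the time question use planned visit contrasts. Use no joint test that mixes primary and secondary outcomes. This also brings the analysis into line with the sample-size calculation, which is for a group by time interaction on the primary outcome.

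The cost is a change of analysis wording, with no effect on sample size or conduct. The downside is more separate results to report in place of one omnibus p-value.
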